## Abstract

**Background:**

More than one-third of cancer-related health information is unreliable or misleading. With increasing health information seeking, the risks of misinformation exposure are growing. Educational approaches that are delivered clearly and in accessible formats are a promising way to strengthen critical thinking and decision-making skills, thereby helping to reduce the exposure of those impacted by cancer to misleading cancer information.

**Methods:**

This pilot randomised trial will assess the feasibility and acceptability of conducting a larger definitive trial evaluating the Informed Health Choices-Cancer (IHC-C) programme. The IHC-C is an online evidence-based education programme co-designed by stakeholders, including public and patient partners. It aims to equip people impacted by cancer (i.e., current patients, survivors, caregivers, and loved ones) with the skills and knowledge necessary to think critically about the reliability of health information and claims and make informed health choices. Participants will be randomised to either the IHC-C intervention group or a waitlist control group. The primary outcome of this pilot trial are feasibility (recruitment and retention rates, etc.) and acceptability (participant satisfaction and perceived usefulness, etc.). Demographic and cancer-related data will be collected to characterise the sample and inform recruitment strategies for a future definitive trial. Preliminary measures of critical thinking and decision-making skills will also be gathered to support the selection of key outcomes for the future trial.

**Discussion:**

This pilot trial will inform the design and conduct of a future definitive randomised trial. Insights gained will inform sample size estimations, refine recruitment strategies, optimise programme delivery, and improve data collection processes, ensuring a robust and scalable approach for the definitive trial.

## 1. Introduction

There were nearly 20 million new cases of cancer in 2022, and it is predicted that new cases of cancer will reach 35 million annually by 2050 [1]. People impacted by cancer have varying information needs throughout their cancer journey – from diagnosis through treatment to survivorship [2,3] – to best manage their health and make informed health decisions [4]. It is reported that one in three patients actively search for information themselves [5]. Among those impacted by breast cancer, more than 90% engage in information scanning through sources such as television, friends, and family, while over 60% seek information online or from healthcare providers [6].

Despite this significant information need, studies have identified cancer as one of the most concerning topics regarding the quality of health information [7–13]. The World Health Organization has labelled this an ‘infodemic’ of misinformation, defined as information that is inaccurate, outdated, incomplete, or misleading based on the best available evidence at the time, disseminated regardless of intent to mislead [14–16]. Notably, 52% of those impacted by cancer encounter conflicting information [17], and it is concerning that lower-quality and misleading content often garners more engagement than accurate information [12].

The widespread accessibility and rapid dissemination of health information makes it challenging to distinguish reliable from unreliable claims [18–20]. On an individual level, misplaced trust in unreliable claims can lead to delays in standard treatment and avoidable harm, including death. On a collective public level, misinformation about maintaining or improving health can and has altered attitudes, behaviours, and policies on crucial health issues, including cancer, leading to poorly informed choices.

Various strategies have been proposed to combat cancer misinformation, including collaboration with clinicians [21], direct participation of health professionals in social networks [22], and collaborative dialogue between healthcare providers, patients, researchers, and advocacy groups [23]. While health professionals play a crucial role in identifying misinformation, their efforts are limited by the sheer volume of misinformation. Consequently, the burden of identifying misinformation falls heavily on those impacted by cancer themselves [12].

While reducing the amount of information available may not be possible, education programmes have been suggested as an effective way to reduce the number and extent to which those impacted by cancer are exposed to or impacted by misinformation [14,16,24,25]**.** Low health literacy is associated with greater use of and trust in health information on social media [26]; therefore, such programmes seek to improve health literacy and enable better informed decision-making [6,27,28].

The Informed Health Choices-Cancer (IHC-C) programme [29–32] is an evidence-based online education initiative designed to equip individuals impacted by cancer with the skills and knowledge needed to critically assess the reliability of health claims and make informed decisions. The programme was systematically developed through a rigorous, multi-phase process that included stakeholder engagement, prioritisation of Key Concepts, co-design of content, and iterative pilot testing with refinement based on participant feedback. The programme is now ready for evaluation as an intervention in this randomised controlled trial (RCT).

This pilot RCT protocol details a trial to investigate the feasibility and acceptability of conducting a definitive trial of the effectiveness of the IHC-C programme. Data will be collected to inform the design and methodology of the definitive RCT.

## 2. Methods

### 2.1. Study design

This pilot randomised trial will investigate the feasibility and acceptability of conducting a definitive trial of the IHC-C programme. This protocol’s reporting follows the Standard Protocol Items: Recommendations for Interventional Trials (SPIRIT) guidelines (S1 File) [33]. The trial design adheres to the Consolidated Standards of Reporting Trials (CONSORT) statement and its adaptation for pilot trials and eHealth interventions [34–36]. Fig 1, developed in accordance with the SPIRIT reporting guidelines and adapted to the design of this pilot trial, presents the schedule of enrolment, interventions, and assessments. Fig 2 outlines the study flowchart, which will be presented in the publication of trial results.

**Fig 1 pone.0333871.g001:**
[figure not shown]
Schedule of enrolment, interventions, and assessments.

**Fig 2 pone.0333871.g002:**
[figure not shown]
Flowchart.

### 2.2. Participants

Based on the previous stages of the IHC-C programme development, which involved stakeholder-led prioritisation and pilot testing with people impacted by cancer [31], we will recruit:

Current patients of any type of cancer,Survivors of any type of cancer,Informal caregivers of a person with cancer,Loved ones of a person with cancer.

#### 2.2.1. Inclusion criteria.

Age ≥ 18 years,Current patients and survivors – diagnosed with any type of cancer,Current patients – person currently undergoing treatment for any type of cancer,Survivors – those who have completed treatment and with or without current care/follow-up,Informal caregivers – those that provide the majority of unpaid, informal care, and self-identify as informal caregiver for a person diagnosed with cancer,Loved ones – family member, friend, or someone who cares about a person diagnosed with cancer, and who self-identifies as a loved one of a person diagnosed with cancer,Be able to commit to the study for at least four weeks,Can give informed consent,Can access the internet.

#### 2.2.2 Exclusion criteria.

Currently involved in another similar study,Irregular and frequently changing caregivers (for informal caregivers).

### 2.3. Recruitment and obtaining informed consent

Recruitment is expected to take place between May and October 2025. Participants will be recruited through convenience sampling, utilising both online and offline methods. Online recruitment will involve targeted social media campaigns on suitable platforms, where posts will be designed to engage individuals impacted by cancer. The posts will direct potential participants to an online expression of interest portal. Offline efforts will include traditional media campaigns through press releases distributed to local and national media outlets. These releases will raise awareness about the trial within the broader community, particularly among those who may not be active online. Additionally, recruitment will be bolstered by outreach through cancer support centres, organisations, charities, and groups.

Interested individuals will be directed to an online survey where they can submit their email addresses. Participants who express interest will be emailed further information and an online consent form. Confidentiality and secure data handling practices will be clearly communicated at this stage.

### 2.4. Sample size

Following guidance for pilot trials [37–40], we will recruit 30 participants per group to allow for an anticipated 15%−25% attrition rate [32]. This target will provide sufficient numbers (20–25 participants per group) for assessing feasibility outcomes including recruitment, retention, and adherence rates [41–45].

### 2.5. Randomisation

After informed consent and baseline data collection, participants will be randomised to study arms using stratified randomisation based on cancer experience (current patients, survivors, informal caregivers, and loved ones) to ensure balanced representation across these groups. Participants will be randomly assigned in a 1:1 ratio to either the IHC-C intervention group or the waitlist control group through the QuestionPro survey platform [46]. To implement stratified randomisation, separate block paths will be configured in the platform’s survey logic for each stratum, with each stratum identified based on participants’ responses to a question about their cancer experience. Within each stratum-specific block, the platform’s automated block randomisation feature will be used, with the “evenly present blocks” setting enabled to maintain balance between groups to make sure the randomisation occurs independently within each stratum, consistent with standard stratified randomisation procedures, and reduces the risk of allocation imbalances that can occur in small-sample pilot trials. Allocation will remain concealed from researchers throughout the process.

Based on earlier recruitment for this programme, we anticipate a higher proportion of survivor respondents [32]. To avoid excluding these volunteers while still preventing extreme imbalance, we will not impose fixed numeric quotas per stratum. Instead, stratified randomisation will continue until the overall sample reaches N = 60. If any stratum remains under-represented (≤ 10 participants) when total enrolment nears 50, targeted advertising will be used to bolster that subgroup.

### 2.6. Blinding

Participants and study researchers will be blinded to group allocation at the time of recruitment and baseline assessments, as randomisation will occur only after these assessments are completed. However, for practical reasons, researchers will not remain blind to the allocation after randomisation, and participants will be informed of their group allocation – whether or not they are allocated to receive the intervention – immediately following randomisation. Due to the nature of the intervention, outcome assessors cannot be fully blinded, which will be acknowledged as a study limitation.

### 2.7. Intervention

#### 2.7.1. Informed Health Choices-Cancer programme.

The IHC-C programme was developed collaboratively with public and patient involvement (PPI) participants, oncologists, cancer nurses, cancer researchers, and educators. An ongoing iterative process of drafting, reviewing, revising, and refining ensured that the programme’s content was clear, comprehensible, and aligned with high educational standards while effectively communicating the intended learning outcomes. The programme underwent two rounds of pilot assessments with these key stakeholders before implementation in this trial.

The IHC-C programme is a nine-unit online educational programme (see Fig 3) developed using a human-centred design (HCD) approach with iterative refinement cycles. It aims to help people impacted by cancer think critically about the reliability of health information and claims and make well-informed choices [32]. Hosted on the Moodle learning management system (LMS), the programme can be freely accessed from any location or device with internet access (see Fig 3).

**Fig 3 pone.0333871.g003:**
[figure not shown]
IHC-C programme on Moodle.

The nine units are derived from a suite of 49 Informed Health Choices (IHC) Key Concepts (KC), prioritised by the first stage of the IHC-C project for their relevance to those impacted by cancer [32]. The intervention has been designed based on evidence that incorporates various educational formats, such as narrated texts, videos, online articles, social media posts, and interactive activities, to provide comprehensive, relevant, cancer-specific information and knowledge. Each unit is on a specific topic and follows a consistent structure (see Fig 4), requiring 40–45 minutes of study time.

**Fig 4 pone.0333871.g004:**
[figure not shown]
IHC-C programme units.

Participants can revisit each unit multiple times, with their progress and responses saved. Each unit concludes with a multiple-choice quiz related to the unit’s topic and learning outcomes. All participants are encouraged to complete the quiz, and correct answers with explanations are provided afterwards. Quiz results will be used to assess participants’ learning outcomes, while completion is encouraged, non-completion will not affect their participation in the programme. If participants experience difficulty completing the quiz (e.g., due to illness, literacy, or technical issues), they will be offered appropriate support or an alternative way to provide feedback.

#### 2.7.2. Intervention group.

Participants randomised to the intervention group will be given access to the IHC-C programme after allocation. The intervention will occur over four weeks. Participants will be encouraged to follow the intervention instructions and complete the programme at their own pace within the four weeks. Those who have not started or completed the programme will receive a follow-up email reminder at the beginning of the final week. Additional support will be offered to participants who show low engagement early in the intervention period, including automated reminders and, where appropriate, personalised follow-up emails to encourage ongoing participation. Email support will be available to all participants, with responses typically provided within 24 hours. A certificate of completion will be awarded to those who finish the programme.

#### 2.7.3. Waitlist control group.

Participants assigned to the waitlist control group will gain access to the IHC-C programme after four weeks, once the intervention group completes the programme and assessments. Participants in the waitlist group will then have four weeks to complete the programme, during which they will receive the same support, reminders, and resources as those in the intervention group. All data collection, including baseline and follow-up assessments, will be conducted using the same tools and methods to ensure comparability of outcomes across both groups. As the primary aim of this pilot study is to inform the design of a future definitive trial, this waitlist control design allows for a controlled comparison of feasibility and acceptability between groups during the intervention phase, while ensuring that all participants ultimately receive access to the programme.

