#### 2.8.4. Assessment timeline.

Assessments will occur at four time points (see Fig 1):

T − 1 (Baseline assessment): All participants will complete baseline assessments.T0 (Allocation): Randomisation and assignment to the intervention or waitlist control group. No assessments are conducted at this timepoint.T1 (Post-intervention: 4 weeks): Both groups complete assessments – intervention group after completing the programme, control group without programme access.T2 (Control access: 6 weeks): Waitlist control group receives programme access.

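### Waitlist access is tied to the intervention group finishing, not to the control's own T1, and sections 2.7.3 and 2.8.4 disagree on when it opens

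*Protocol article*

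**What the plan says.** Allocation is individual: "After informed consent and baseline data collection, participants will be randomised to study arms using stratified randomisation" (section 2.5), and randomisation goes on until 60 participants are enrolled. "Recruitment is expected to take place between May and October 2025" (section 2.3). "Participants randomised to the intervention group will be given access to the IHC-C programme after allocation", and "The intervention will occur over four weeks" (section 2.7.2).

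For the waitlist arm, section 2.7.3 says that controls "will gain access to the IHC-C programme after four weeks, once the intervention group completes the programme and assessments". It sets two conditions, elapsed time and completion by the other arm. Neither refers to the control's own assessment.

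Section 2.8.4 describes T1, at 4 weeks, as follows: "Both groups complete assessments – intervention group after completing the programme, control group without programme access". It then lists a separate later step: "T2 (Control access: 6 weeks): Waitlist control group receives programme access".

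The comparison that depends on T1 is in section 2.9.3, which compares mean changes in critical thinking, decision-making and eHealth literacy between the arms at the end of the intervention. Section 2.9 states an intention-to-treat analysis.

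**The concern.** T1 is the one assessment at which the arms are meant to differ in exposure. Section 2.8.4 states that condition, but the switching rule in section 2.7.3 does not secure it, because access can open whether or not the control has answered. All data are collected online (section 2.10), so late returns are foreseeable. Under intention-to-treat, a late control who has already used the programme stays in the control arm, and that pulls the difference towards zero. The abstract says the pilot will inform sample size estimation, so a diluted difference could carry into the definitive trial.

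The trigger also refers to a group. With individual randomisation over several months, completion by the intervention group is not an event on any one control's clock. The section does not say whether it means the matching four-week period or the whole arm.

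**Working it through.** **Inputs.** T1 at 4 weeks and control access at 6 weeks (section 2.8.4); control access after four weeks (section 2.7.3); programme length of four weeks (section 2.7.2); recruitment May to October 2025 (section 2.3); 30 per group with 15-25% attrition (section 2.4). The documents give no rate of late T1 return.

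**Step 1: gap between T1 and access, per-participant reading.** Gap = access week - T1 week.
- Section 2.7.3: 4 - 4 = 0 weeks. Any control who answers after access opens can do so with the programme available.
- Section 2.8.4: 6 - 4 = 2 weeks. Only a control more than two weeks late is affected.

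The two sections do not give the same access time. Under either one, access is not conditional on a submitted T1.

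**Step 2: wait for access, arm-level reading.** Wait = (last intervention randomisation + 28 days) - control's randomisation.
- Widest case, control on 1 May and last intervention participant on 31 October: 183 + 28 = 211 days, and 211/7 = 30.1 weeks (access about 28 November).
- Narrower case, control on 31 May and last intervention participant on 1 October: 123 + 28 = 151 days, and 151/7 = 21.6 weeks.

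Neither wait fits four weeks or six weeks.

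**Step 3: do the two problems coincide?** No. An early control who waits 20 to 30 weeks has T1 long behind before access opens, so that T1 is not exposed. Exposure at T1 needs the per-participant reading; the long wait needs the arm-level reading.

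**Step 4: possible dilution, per-participant reading.** Let f be the share of responding controls who answer T1 after access and have already gained the full effect D. The expected observed difference is D - fD = (1 - f)D. Retained controls number 30 x 0.75 = 22.5 to 30 x 0.85 = 25.5.

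| f (assumed) | Controls affected | Share of true difference left |
|---|---|---|
| 10% | 2.3 to 2.6 | 90% |
| 20% | 4.5 to 5.1 | 80% |
| 30% | 6.8 to 7.7 | 70% |

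For any given f these are upper bounds on the loss. The programme has nine units of 40-45 minutes (sections 2.7.1 and its figure text), that is 9 x 40 = 360 to 9 x 45 = 405 minutes, or 6 to 6.75 hours. A control who has only just gained access is unlikely to have had the full effect.

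**The case against.** The strongest reply is that the assessment timeline already orders the events correctly. It has controls answering T1 unexposed and lists access as a later step two weeks on. A reader might infer from section 2.7.3 alone that the plan has controls answering T1 with the programme open. The documents do not support that: section 2.8.4 says the opposite. What is missing is the rule that would enforce the order for late responders.

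The second reply is that the arm-level reading is strained. Allocation, intervention access and the timeline all run per participant, and a wait of months contradicts the four weeks in the same sentence. This has force. If the clause means the matching four-week period, the rolling-enrolment problem disappears, but the zero gap of Step 1 then applies. A reader might add the two harms together, and Step 3 shows that this is wrong.

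Third, the exposed contrast is a secondary comparison in a pilot whose primary criteria are descriptive (section 2.9.2), and the share of late controls is not known. Both points stand, and they limit the weight of the finding.

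Fourth, how late responders are handled could be left to the full protocol, and the schedule in Fig 1, which I have not seen, may settle the timing. That would not cure the wording of section 2.7.3, which states a trigger unrelated to the control's T1 and an access time different from section 2.8.4.

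**Conclusion.** The point holds in a limited form. Section 2.7.3 fixes control access by elapsed time and the other arm's completion, which does not protect the condition that section 2.8.4 sets for control T1, and the two sections disagree on the access time. Depending on the reading, the result is either no gap between T1 and access, or a wait of up to about 30 weeks for early controls, but not both.

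The dilution cannot be sized from the documents. The 90-70% range rests on an assumed late share of 10-30% and on full benefit before T1; with partial exposure the loss is smaller. It concerns the secondary comparison in section 2.9.3. A reader might infer that the feasibility and acceptability conclusions are undermined. The documents do not support that, because those criteria are judged descriptively against fixed thresholds. The change is worth making because the remedy is cheap and the pilot's estimates are meant to feed the definitive trial.

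**What to change.** - Reconcile sections 2.7.3 and 2.8.4 on when controls gain access, and state that the time is counted from each participant's own randomisation. Which access time applies is for the sponsor to settle.
- In section 2.7.3, replace the group trigger with an individual one: access opens no earlier than the reconciled time, and only once that control's T1 is submitted or a fixed T1 response window has closed. Closing the window ensures that every control still receives the programme.
- Record the T1 date and the access date for each control.
- Keep every T1 value in the intention-to-treat analysis, flag those returned after access, and add a sensitivity analysis that sets them to missing and handles them by the multiple imputation already planned in section 2.9. Simply discarding them would remove participants from one arm only, on a post-randomisation event, against the stated principle.

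**Cost.** This takes a few sentences of wording, two dates per control and one extra analysis. A few late responders would gain access slightly later. Making access wait on T1 also gives controls, and only controls, an incentive to complete it, which could raise the completion rate judged against the 90% data-collection criterion in section 2.9.2. That criterion should therefore also be reported by arm.
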